### Trial design and study setting

2.1

The trial is designed as a single-arm, non-randomized, open, exploratory clinical one. The protocol was written in accordance with Standard Protocol Items: Recommendations for Interventional Trials 2013 statement.^[15]^ The study protocol was approved by The Medical Ethics Committee of Longhua Hospital, Shanghai University of Traditional Chinese Medicine (No: 2020LCSY021), and informed consent will be obtained from each participant.

The trial will be conducted in Longhua Hospital, Shanghai University of Traditional Chinese Medicine, from July 2020 to June 2021 and 30 qualified participants will be recruited from public and will be allocated to the therapy group for 2 months. The flowchart is shown in Figure 1, and the timeline is given in Table 1.

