#### Inclusion criteria

2.2.1

Participants who meet all the following criteria will be recruited:

1.Aged between 18 to 65 years old, both genders;2.Meet the diagnostic criteria of MS:^[16–18]^① Overweight or Central obesity: BMI cut-off point for obesity (>24.0 kg/m^2^) or waist circumference ≥90 cm for males and ≥85 cm for females.② Hyperglycemia: fasting plasma glucose (FPG) ≥6.1 mmol/L (110 mg/dl) or 2 hour plasma glucose ≥7.8 mmol/L (140 mg/dl), or previously diagnosed type 2 diabetes.③ Hypertensive: systolic blood pressure ≥130 or diastolic blood pressure ≥ 85 mm Hg, or treatment of previously diagnosed hypertension.④ Raised TG level: fasting TG level≥1.7 mmol/L (150 mg/dl), or received treatment for this lipid abnormality.⑤ Reduced HDL-c: fasting blood HDL-c<0.9 mmol/L (35 mg/dl) for males and <1.0 mmol/L (39 mg/dl) for females.^∗^with 3 or all of the above 5 items can be diagnosed as metabolic syndrome.3.Agree to join this clinical study, volunteer to sign up informed consent form and agree to participate in all visits and inspections in accordance with the requirements of the study protocol.

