### Outcome measurements

2.4

Outcome will be performed by laboratory tests or physical examination after the intervention (at week 8).

Primary outcome will be the change of blood lipid and glucose which are the most intuitive assessments of the body. Main assessments of blood lipid includes TG, 3total cholesterol, HDL-c, low density lipoprotein cholesterol, free fatty acid and FPG.

Other outcomes are body weight and BMI. Weighing the body weight to see if there is any weight loss. Using the following formula to calculate BMI: Body weight in kilograms divided by height in meters squared. Recording body weight and calculating BMI at each visit, namely every 2 weeks. The evaluation will be performed in baseline and treatment endpoint. In addition, the researchers will keep in touch with participants via phone call, message or through the Internet to ensure the progress every day.

Baseline observation include demographic data (age, gender, occupation, education level), medical history, allergies history, past or combined medication, height, waist circumference. Assessments include clinical laboratory examination (TG, total cholesterol high-density lipoprotein cholesterol, low density lipoprotein cholesterol, free fatty acid and FPG), body weight, BMI, and safety assessments. Adverse events will be recorded throughout the study. Researchers will evaluate the severity of the adverse event and decide whether to continue the treatment or not. Participants with adverse events will receive necessary medical interventions. Participants who quit the study due to untolerable reactions or uncontrollable conditions will enter into the follow-up period after the last treatment. All participants will enter into the follow-up period for 4 weeks at the end of the treatment.

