### Determination of sample size

2.5

The trial is a single-arm, non-randomized, open, exploratory clinical trial. For exploratory and safe considerations, it is designed as a small sample trial. The sample size cannot be calculated due to lack of database. For the determination of participants recruited in this trial, after consulting with experts in this field, we finally designed the sample size to 30 (n = 30).

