### Statistical analysis

2.6

In the trail, Statistical Product and Service Solutions software will be applied to conduct statistical analysis. A full analysis set will be considered as the principal analysis and the per-protocol is set as the subset of full analysis set. The per-protocol will consist of participants who perform the study and have principal variable base-line values in this trial. The principal parameters will be conducted at baseline, each treatment and in the follow-up period.

Descriptive statistics will be used to balance baseline and parametric characteristics. Researchers will compare and analyze the data from baseline to the end of the follow-up period to confirm the difference between primary and other outcomes. When it comes to normal distribution, one-way analysis of variance will be used to compare subjective and semi-objective outcomes. Otherwise, it will be run by rank sum test. In the efficacy comparison stage, the outcome measurements before and after the intervention will adopt single factor analysis. For each outcome, *P* < .05 is considered statistically significant.

Multi-group correlation analysis include extraction and sample derivation of metabolites (blood samples and stool samples). GC-MS analysis Metabolomics instrumental analysis will be performed on an Agilent 7890A gas chromatography system coupled to an Agilent 5975C inert MSD system (Agilent Technologies Inc., CA). Principal component analysis is used to truly reflect the differences between groups, if the differences between groups are small, then the supervised model, namely Partial least squares-discriminant analysis will be used to eliminate interference. It will also adopt Student *t* test to identify differential metabolites and analyze correlation matrix.

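### Section 2.6 lets an unspecified normality check choose between two tests, both for independent samples, although the primary data are before/after pairs; one paired analysis per outcome should be fixed in advance

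*Protocol article*

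**What the plan says.** The protocol article, section 2.1, sets the design: "The trial is designed as a single-arm, non-randomized, open, exploratory clinical one". Section 2.5 explains the size: "The sample size cannot be calculated due to lack of database", and after expert advice "we finally designed the sample size to 30 (n = 30". No effect size, SD or power is given.

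Section 2.4 makes change in blood lipids and glucose the primary outcome and lists six laboratory values: "Main assessments of blood lipid includes TG, 3total cholesterol, HDL-c, low density lipoprotein cholesterol, free fatty acid and FPG". Table 1 schedules these six at enrolment and Week 8 only, so each participant contributes one pair per outcome.

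Section 2.6 then states the method: "When it comes to normal distribution, one-way analysis of variance will be used to compare subjective and semi-objective outcomes". The next sentence gives the alternative: "Otherwise, it will be run by rank sum test". A further sentence assigns the before/after efficacy comparison to a single-factor analysis without defining it. The decision criterion is "For each outcome, *P* < .05 is considered statistically significant". The section names no normality test, threshold, variable to be checked or transformation, and does not say that the comparison is paired.

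**The concern.** Two things in the stated method are unsatisfactory.

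- **The test is chosen from the data to be tested.** With six primary outcomes and 30 people, some outcomes may go to ANOVA and others to a rank test, partly by chance. For a before/after question what matters is the distribution of the within-person change, and the text does not say that this is what is examined.
- **Both branches are independent-sample methods.** One-way ANOVA with time as the factor, and the rank sum test, treat the 30 baseline and 30 Week 8 values as coming from 60 different people. The within-person correlation is then discarded.

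The trial is exploratory, and its Discussion says the result will be used for further studies. Its most useful product is an estimate of change with its variability. A rule that ends in a P value from a method that varies by outcome serves that purpose poorly.

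Skew is plausible for some outcomes. The TG criterion is "fasting TG level≥1.7 mmol/L (150 mg/dl), or received treatment for this lipid abnormality", which is one of five criteria of which three suffice, and no upper limit is set. Normal, treated and very high values can therefore be mixed.

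**Working it through.** The plan has no power figure to reproduce, so the check is a simulation supported by hand calculation.

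**From the article:** n = 30, one pair per outcome, P < .05 per outcome (taken as two-sided).

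**Assumed, not in the article:** log-normal values; log-SD σ of 0.5 (TG-like skew) or 0.2 (mild skew); baseline to Week 8 correlation ρ of 0.5 or 0.7 on the log scale; Shapiro-Wilk at 5% as the normality check; true Week 8/baseline ratio 0.80 (σ = 0.5) or 0.92 (σ = 0.2). There were 4,000 simulated trials per setting.

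**Rules compared:** (a) ANOVA/rank sum switch on the values, unpaired as worded; (b) paired t/signed-rank switch on the raw change; (c) fixed paired t test on log(Week 8/Week 0).

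**How often normality is rejected, and power:**

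| σ | ρ | True ratio | Values rejected (either visit) | Change rejected | Power (a) | Power (b) | Power (c) |
|---|---|---|---|---|---|---|---|
| 0.5 | 0.5 | 0.80 | 91% | 34% | 35% | 61% | 66% |
| 0.5 | 0.7 | 0.80 | 89% | 40% | 31% | 81% | 87% |
| 0.2 | 0.5 | 0.92 | 32% | 8% | 32% | 60% | 60% |
| 0.2 | 0.7 | 0.92 | 32% | 9% | 28% | 81% | 82% |

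**Type I error (true ratio 1):** (a) 0.05 to 0.9%; (b) 4.7 to 6.0%; (c) 4.7 to 5.5%.

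**Hand check of (c), σ = 0.5.** The SD of the log ratio is σ√(2(1−ρ)), and the non-centrality is |ln 0.80|·√30/SD, with ln 0.80 = −0.2231.

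- ρ = 0.5: SD = 0.500; 0.2231 × 5.477/0.500 = 2.44; power from the non-central t with 29 df is 0.66.
- ρ = 0.7: SD = 0.387; 0.2231 × 5.477/0.387 = 3.16; power 0.86.

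**Hand check of (a), on the log scale.** An unpaired test uses a standard error of σ√(2/30) = 0.5 × 0.258 = 0.129, so it needs a difference of 2.00 × 0.129 = 0.258. The true standard error is SD/√30.

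- ρ = 0.5: true SE 0.0913; (0.258 − 0.223)/0.0913 = 0.39; power about 0.35.
- ρ = 0.7: true SE 0.0707; (0.258 − 0.223)/0.0707 = 0.50; power about 0.31.

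Under no effect, the critical value 2.00 corresponds to 2.00/√(1−ρ) true standard errors, which is 2.83 or 3.65. The tail probabilities are about 0.5% and 0.03%, close to the simulated 0.7% and 0.05%. The unpaired rule is therefore very conservative.

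**Reading the results.** The method chosen depends heavily on what is checked: at σ = 0.5, values are called non-normal in about 90% of trials and changes in 32 to 40% (null settings included). Pairing accounts for most of the power difference: from (a) to (b) is 26 to 50 points at σ = 0.5, and from (b) to (c) a further 5 to 6. At σ = 0.2 the step from (b) to (c) is 0 to 1 point here; a repeat simulation put it at about 2.

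**The case against.** **The switch may not govern the primary outcomes.** Its sentence speaks of subjective and semi-objective outcomes, and the before/after comparison has its own sentence. But section 2.4 lists no subjective outcome, only laboratory values, weight and BMI. Either the switch applies to these or it applies to nothing. If the single-factor sentence governs instead, it most likely means the same one-way ANOVA, and the same remedy applies. The ambiguity is real, and it is a reason to rewrite the section.

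**Detail may sit in the full protocol or SAP.** This is right for the normality procedure, transformations, estimates and intervals; their absence from an article is no fault. What stands is what the article does state: a distribution-dependent choice between two independent-sample tests. The authors may mean paired versions under loose names, in which case the power loss disappears and only the wording needs repair.

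**Three stronger readings are tempting and not supported.**

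- A reader might infer that normality is checked on the raw values. The text names no scale and does not exclude changes or logs.
- A reader might infer that a rank-tested outcome will have no effect size. Nothing bars a median change or a Hodges-Lehmann estimate beside the test.
- A reader might infer that the switch inflates false positives. The simulation shows it does not.

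**The log-ratio gain is partly built in.** Log-normal data with a proportional effect are the case for which the log-ratio t test is best. With a skewed baseline (median 2, log-SD 0.3 to 0.5) but an additive change of 0.3 and additive within-person noise (SD of change 0.6), the log ratio had 65 to 67% power against 73 to 76% for the paired switch, a loss of 6 to 10 points. This stands: the sign of the gain depends on a proportional response that the article does not establish.

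**Mixed scales remain.** Using logs for some outcomes and original units for others still leaves different scales. That is true, but they would be chosen beforehand and not from the results.

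**Conclusion.** The point holds in a limited form and should be corrected. Section 2.6 makes the method depend on an unspecified look at the distribution, so the six primary outcomes may be analysed differently, and both named methods ignore the pairing.

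Unpaired analysis is the costly part. Under the assumed σ = 0.5 and a 20% fall, power is about 31 to 35% (31 to 34% in a repeat simulation), against 61 to 81% with paired tests and the same switch. The switch alone costs little. Replacing a paired switch by a fixed log-ratio test gains about 5 points with TG-like skew and two or less with mild skew, and can lose power if the response is additive. It would be wrong to conclude that power is necessarily lost on the outcomes of interest because logs are not used.

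All power figures rest on the assumed distribution, correlations and effects. That the named tests do not match paired data does not depend on those assumptions.

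**What to change.** In section 2.6, delete the normality switch and the undefined single-factor wording, and name one paired analysis for each outcome before the data are seen:

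- Default: the within-person Week 8 minus Week 0 change in original units, with a one-sample t test and 95% CI.
- For outcomes expected to be right-skewed, such as TG: the within-person log(Week 8/Week 0), tested in the same way and reported as geometric mean percent change with 95% CI. List these outcomes by name.
- For every outcome: the Wilcoxon signed-rank test as sensitivity analysis, not as a replacement chosen from the data.

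The cost is a few sentences; no visit, sample or measurement changes. The downside is that some outcomes are reported as percent change and not in mmol/L, and that the log scale is an advantage only if the response is roughly proportional. If that is doubted for an outcome, the plain paired difference fixed in advance also removes the data-driven choice.

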### Quality control

2.7

Main researchers in this trial will be asked for Good Clinical Practice certificates and the other researchers will receive relevant training on the qualifications required for clinical trials to ensure the quality of the research. All researchers will perform operations in accordance with Standard Operating Procedures to make sure the consistency of the research. The test results will be saved in the original documents, laboratory results and records. The original data will be registered in the electronic case report form (e-CRF) and the data uploaded in the e-CRF is parallel to the original data. Kernel researchers will verify the accuracy of the original data. The data will be analyzed independently by different statisticians. The data may be used to do interim analyses, and the monitor will supervise the whole study period and make the final decision if terminate the trial.

All participants will be collected blood samples and stool samples at the research hospital site when participating in the study for the first time. The laboratory will assist in the collection of samples, and the main researchers will collect and evaluate the samples. Longhua Hospital, Shanghai University of Traditional Chinese Medicine will provide sample processing, aliquoting and storage facilities. All samples will be placed in the storage warehouse of the hospital after centrifugal extraction, and stored in a liquid nitrogen refrigerator at -80°C. All samples will be coded with a unique number. Any process involving sample transfer will strictly abide by the sample transfer operating specifications. These processes will be supervised by the Medical Ethics Committee of Longhua Hospital.

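### The rule that moves from PCA to supervised PLS-DA when differences look small can, unless validated, turn noise into apparent separation; the metabolite t test is stated without pairing

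*Protocol article*

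**What the plan says.** The last paragraph of section 2.6 of the protocol article describes the metabolomics, which covers "extraction and sample derivation of metabolites (blood samples and stool samples"). PCA comes first, as the method meant to show the real group differences. The next step depends on what PCA shows: "if the differences between groups are small, then the supervised model, namely Partial least squares-discriminant analysis will be used to eliminate interference". For single metabolites the article says: "It will also adopt Student *t* test to identify differential metabolites and analyze correlation matrix". It does not say whether that test is paired.

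Three other statements bear on this. Section 2.1: "The trial is designed as a single-arm, non-randomized, open, exploratory clinical one". Section 2.5: "we finally designed the sample size to 30 (n = 30"). Section 2.7, on when the samples are taken: "All participants will be collected blood samples and stool samples at the research hospital site when participating in the study for the first time". Table 1 has no row for metabolomics sampling, and the article does not define the groups that PCA and PLS-DA are to compare. The Abstract and the Discussion both name exploration of the mechanism of action as an aim of the trial.

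**The concern.** PCA does not use the group labels; PLS-DA does. When there are many variables and few samples, PLS-DA can nearly always find a combination of variables that splits two labelled sets, whether or not they differ. The printed rule calls on PLS-DA precisely when the unsupervised view shows little difference, and describes the step as cleaning the data. A reader who follows the rule and looks at the fitted score plot may see clear separation where there is none.

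The t test raises a second, smaller issue. With one arm, the evident comparison is of each participant with themselves. A plain two-sample test does not fit such data.

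What is at stake is the mechanism result: the claimed separation, the list of differential metabolites and the correlation matrix. The lipid, glucose, weight and safety results do not depend on it.

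**Working it through.** The plan gives no power, effect size or metabolite count, so there is no stated figure to reproduce. The check asks what the printed rule does when nothing changes.

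**Inputs from the protocol article:** 30 participants (2.5); one arm (2.1); PCA, then PLS-DA if differences are small (2.6); Student t test (2.6).

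**Assumptions:** two samples per person, before and after treatment (60 in all); 50 to 500 metabolites; within-person correlation ρ of 0 or 0.5; two PLS-DA components on autoscaled data; two-sided 0.05 for the t test.

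**Step 1: PLS-DA on pure noise.** There were 100 simulated data sets per setting, with no true change in any metabolite. Fitted results are compared with 7-fold cross-validation that keeps both samples of a person in the same fold. R²Y is the fitted share of label variance explained; Q² is its cross-validated counterpart. Entries are means.

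| ρ | Metabolites | Label variance explained by first two PCA components | Fitted R²Y | Fitted accuracy | Cross-validated accuracy | Q² |
|---|---|---|---|---|---|---|
| 0 | 50 | 3.6% | 0.63 | 90% | 51% | −0.59 |
| 0 | 100 | 3.4% | 0.82 | 98% | 49% | −0.58 |
| 0 | 200 | 3.7% | 0.94 | 100% | 49% | −0.31 |
| 0 | 500 | 2.9% | 0.99 | 100% | 50% | −0.11 |
| 0.5 | 50 | 0.7% | 0.47 | 82% | 50% | −0.80 |
| 0.5 | 100 | 0.5% | 0.71 | 94% | 50% | −0.77 |
| 0.5 | 200 | 0.3% | 0.88 | 99.5% | 50% | −0.52 |
| 0.5 | 500 | 0.2% | 0.96 | 100% | 50% | −0.23 |

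PCA shows almost nothing on noise (0.2% to 4%), so the switch would be triggered. The fitted PLS-DA then separates the labels at 82% or better, even at 50 metabolites, where there are still fewer variables than samples. Validation by person brings it back to chance.

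**Step 2: t test with the correct size** (paired test, or truly independent samples). Expected false flags = 0.05 × number of unchanged metabolites: 0.05 × 100 = 5; 0.05 × 200 = 10; 0.05 × 500 = 25.

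**Step 3: unpaired t test on before-after pairs.** The test takes the variance of the mean difference to be 2σ²/30. The true value is 2σ²(1 − ρ)/30. At ρ = 0.5 the standard error is overstated by 1/√0.5 = 1.41, and the per-test error falls from 5% to about 0.6–0.8%. Simulated false flags were 0.8, 1.3 and 3.3 at 100, 200 and 500 metabolites; the paired test on the same data gave 5.2, 10.2 and 24.7. The unpaired test is therefore conservative here, and it loses power to find real changes.

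**The case against.** The strongest reply is that looking with PLS-DA after an uninformative PCA is not wrong in itself. PCA shows the directions of largest variance, which in before-after data may simply be differences between people, so a flat PCA is not a negative test. Validation exposes false separation, as the table shows, and a condensed article may leave validation and multiplicity control to the full protocol or SAP. The analysis is also exploratory.

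Much of this stands. A reader might infer that no validation or multiplicity correction is planned, or that every metabolite will be tested unadjusted. The article says neither. Its threshold, "For each outcome, *P* < .05 is considered statistically significant", closes the paragraph on clinical outcomes; metabolites are not among the outcomes in section 2.4, and the metabolomics paragraph gives no threshold. A reader might also combine 5, 10 or 25 false flags with the complaint that pairing is ignored. Steps 2 and 3 show that these do not go together if the samples are positively correlated pairs. Nor can one say that most reported metabolites would be false: that depends on how many truly change, and a pure-noise simulation makes every discovery false by construction.

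What does not fall is the printed rule. Its trigger and its rationale are stated, not omitted. A SAP that added validation would improve matters, but one that kept this wording would keep the fault.

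**Conclusion.** The point holds in a limited form. Making PLS-DA conditional on small PCA differences, and describing it as eliminating interference, is a badly fixed rule. Unless the model is validated, the rule can present noise as separation: fitted accuracy of about 82% to 100% at 50 to 500 metabolites, against about 50% when validated by person. It does not follow that it will do so.

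The t test should be stated as paired. At 0.05, a correctly sized test flags about 5% of truly unchanged metabolites; an unpaired one on positively correlated pairs flags fewer and loses power.

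These figures rest on an assumed metabolite count, correlation, number of components and second sampling time. The last needs care. Section 2.7 places sampling at first participation only, and the groups are undefined. A reader might infer that no post-treatment sample exists. The article does not say that, but the text must be reconciled before a before-after analysis can be run.

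This should be corrected. It affects the only analysis described for the mechanism aim, and does not touch the primary outcome, the sample size or safety.

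**What to change.** In section 2.6:

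- Report PCA in all cases. Delete both the condition that triggers PLS-DA and the stated purpose of eliminating interference.
- Report PLS-DA on within-participant differences (multilevel PLS-DA), and only with cross-validation that keeps a participant's samples together and a permutation test, for example with at least 1,000 permutations. Claim separation only if the permutation test supports it.
- Compare metabolites by paired t or signed-rank tests, with Benjamini-Hochberg control of the false discovery rate, for example at 5%.
- State that the groups are the baseline and post-treatment samples of the same participants. Give the time of the post-treatment blood and stool samples and reconcile it with section 2.7 and Table 1.

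The cost is a few sentences and a little computing time. Fewer metabolites are likely to be declared different.
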